#### Observational study

##### Primary outcome

To evaluate frequencies and size of clusters and attack rates in schools, compared with incidence, prevalence, frequency of SARS-CoV-2 positive subjects and clusters in the different waves.

##### Secondary outcomes

To evaluate the psychological health of students and teachers during the COVID-19 pandemics: negative and positive feeling during confinement, behaviour and emotions experienced with respect to preventive measures (masks, social distancing), distance learning, and vaccines. The evaluation will be carried out through standardized questionnaires and ad hoc questions.Number/size of clusters by the usage of different preventive measures adopted in different classrooms by prevalence of different variants and taking into account vaccination rates.Social distancing practices changes along the pandemic and potential association with incidence.Mobility practices changes along the pandemic and potential association with incidence.

### Study design

#### General study design (Fig. 1)

**Fig. 1 Fig1:**
[figure not shown]
Study flowchart. The flowchart summarize the general study where is divided in two sub studies, (i) interventional study which contains a Lolli arm and a control arm; and (ii) observational study. A detailed description have been written in the main text. We want to acknowledge Pez Beta Design for the elaboration of the figure

A multicenter cluster randomised interventional study will be set-up to evaluate the efficacy and applicability of the LM. The study will enrol 440 classes (around 8800 students, teachers and other personnel). Statistical units are represented by classes, randomized to LM or SoC.

The study will be carried out for 6 months, from October 2022 to March 2023 and includes two saliva tests a week. We assume that in the course of the investigated period the incidence rate of SARS-CoV-2 infection will change and this will allow us to test our hypotheses under different epidemiological conditions.

The randomisation will be applied as cluster randomisation: classes will be randomised in each school to the adoption of the LM or to SoC with contact tracing activity by public health departments and regular surveillance based on symptoms indicating testing. The two groups of classes will be compared in order to assess whether the LM will reduce the frequencies of attack rates/clusters dimension compared with classes on SoC. Logistics and costs affordability will also be evaluated.

An observational retrospective and prospective study will be carried out to investigate the prevalence of SARS-CoV-2 in schools with different variants, frequencies and size of clusters and attack rates in schools, the effect of different NPIs on SARS-CoV-2 diffusion in the schools and the related psychological effects. The study will involve classes/schools that are not involved in the interventional randomised study.

### Study population

Kindergartens and school-age children, school personnel and children’s household members.

Schools of all grades have been considered, involving students and all school personnel in order to evaluate the LM in a real environment for its possible deployment and to understand the dynamic of the spread of SARS-CoV-2 infection in the schools.

In case of positive pools, family members of positive individuals will be tested as well, in order to analyse the possible use of schools testing as a sentinel to support the contact tracing analysis, and to evaluate whether the students or school personnel have been infected at school or within their households.

#### Inclusion criteria

Kindergartens and school-age children from public or private schools.Enrolled children may be students of classes that have expressed their consent to participate (no limit of participants per class is adopted).School personnel of participating schools.Household members of participating children/students.Informed consent (for minors the informed consent will be signed by parents or legal guardians).For minors: willingness to participate.

#### Exclusion criteria

No informed consent by schools or children, or the adult participant.Suspicion of acute COVID-19 infection:
In case of unknown respiratory infection, no presence of symptoms that can be attributed to SARS-CoV-2 for at least 48 h.In case of confirmed SARS-CoV-2 infection: exclusion for at least 21 days from PCR-positive diagnosis and no presence of symptoms for at least 48 h.

#### Recruitment and screening

Schools will be selected in collaboration with public health authorities. Letters will be sent to principals, explaining the objective of the two studies and evaluating the interest of schools to participate in one or both the studies.

Once schools have declared their interest to participate, an informative session will be organized with school personnel and representatives of the families and students. Material describing the characteristics of the study will be delivered to the families to explain aims and procedures. Families and students will be asked to sign an informed consent form. Information will be available at a dedicated web page within the EuCARE website (https://eucareresearch.eu).

For the cluster randomised interventional study, classes will be randomized to one of the two groups. At the beginning of each testing session, participants will be screened for exclusion criteria.

#### Assignment to study groups

Classes will be assigned to the study arms with a randomised web-based procedure: the web randomisation module will accept as input the school-class identifier and will provide as output the study arm, based on a randomisation list balanced by four.

The randomisation will be stratified according to age classes (e.g. kindergarten age; primary intermediate school 6–13 years; secondary school).

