#### Determination of sample size

Clusters are defined as epidemiologic links between an index patient and one or more persons who likely acquired SARS-CoV-2 infection in class (i.e., class-associated cases). Given the average infection rates in contacts of about 4% per class [31], a sample size of 440 classes (220 per arm) achieves 80% power to detect a difference between the group proportions of 3.5%. The proportion in arm with LM is assumed to be 4% under the null hypothesis and 0.05% under the alternative hypothesis. The test statistic used is the one-sided Z test with pooled variance with a 5% significance level.

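### With an allocation list balanced by four and arms that cannot be masked, up to one allocation in three could be deduced by anyone who sees the earlier arms in the same list; a school's classes should be locked before any arm is released.

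*Protocol article*

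**What the plan says.** Under Assignment to study groups, the protocol article describes a web procedure. A user gives the module the identifier of a class, and in return it "will provide as output the study arm, based on a randomisation list balanced by four". The only stratifier is age: "The randomisation will be stratified according to age classes (e.g. kindergarten age; primary intermediate school 6–13 years; secondary school". School and country are not named as strata, although General study design says that "classes will be randomised in each school to the adoption of the LM or to SoC with contact tracing activity".

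Under Administration of experimental and control interventions, LM classes give pooled saliva twice a week. Control classes follow usual surveillance, with no sham procedure described. The arm of a class is therefore evident once testing starts.

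The Primary analysis section compares cluster frequencies between arms by a univariate Chi-square or Fisher test.

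**The concern.** A web module hides the list, but it cannot hide an arm that follows from arms already released. In a small constant block, once both places of one arm are used, the rest of the block is known. With unmasked arms, that information is available to whoever can see the earlier allocations.

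Classes are identifiable units with visible differences in risk, such as recent cases or anxious parents. If someone enters classes one by one, chooses the order and sees each arm before the next entry, a particular class can be held back until the wanted arm is due. Consent obtained beforehand does not prevent this, because it does not control the order of entry. Baseline risk could then differ by arm, and the stated primary test does not adjust for it. The article places its confounder-adjusted logistic models under the ancillary observational study. The adjustment described under Handling of missing data concerns response rates, not baseline risk.

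**Working it through.** **Inputs.** Block of four, read as two LM and two SoC (Assignment to study groups). Equal arms, 220 of 440 classes each (Determination of sample size). The article gives no figure for predictability, so there is none to reproduce.

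**Sample size, for context.** The stated difference of 3.5 points from 4% implies 0.5% in the LM arm. With a one-sided 5% level, 80% power and pooled variance, the mean proportion is 0.0225 and n per arm = [1.645·√(2·0.0225·0.9775) + 0.842·√(0.04·0.96 + 0.005·0.995)]² / 0.035² ≈ 221. Power at 220 is 79.8%, so the plan's figure is reproduced. The printed 0.05% would instead give 157 per arm. Neither result bears on the present point beyond confirming the 1:1 ratio.

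**Step 1: forced allocations when every earlier arm is seen.** A 2:2 block has six equally likely sequences.
- AABB and BBAA force positions 3 and 4: two each.
- ABAB, ABBA, BAAB and BABA force position 4 only: one each.

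Total 2·2 + 4·1 = 8 of 6·4 = 24 allocations, or 1/3. On 440 classes that is 440/3 ≈ 147.

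**Step 2: best guess for the same observer.**
- Position 1: 1/2.
- Position 2: guess the other arm, right 2/3 of the time.
- Position 3: certain with probability 1/3, otherwise a coin toss, so 1/3 + (2/3)(1/2) = 2/3.
- Position 4: 1.

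Mean = (1/2 + 2/3 + 2/3 + 1)/4 = 17/24 = 70.8%, against 50% by chance.

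**Step 3: one list shared by k equally active sites.** Each site sees only its own classes but is credited with knowing the block boundaries. An entry is forced only if both used-up places of one arm were seen at the same site.
- Position 3: probability (1/3)(1/k²).
- Position 4: the first three always contain exactly one matching pair, so probability 1/k².

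Forced share = (1/(3k²) + 1/k²)/4 = 1/(3k²).

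| Sites on one list | Forced share |
|---|---|
| 1 | 33.3% |
| 2 | 8.3% |
| 4 | 2.1% |
| 10 | 0.3% |

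Simulation agrees (33.4%, 8.2%, 2.1%, 0.3%). The number of sites per list is an assumption, since the article does not give it.

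**Step 4: what other block schemes would do.** A constant block of 6 forces 1/4 and a block of 8 forces 1/5. Randomly mixed blocks of 4, 6 and 8 with unknown boundaries leave under 1% certain (approximate), but guessing the arm that is behind is still right about 68% of the time. Varying the blocks removes certainty and little of the guessing advantage.

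**The case against.** A reader might infer that one allocation in three is known in advance. The article does not support that. It gives an input and an output for the module. It does not say that classes are entered singly, who enters them, who chooses the order, or whether each arm appears before the next entry. Those are operating details that an article may leave to the full protocol (version 1.1, not shown), so their absence is no finding. The words block and fixed do not appear either, though constant 2:2 blocks are the natural reading. With age as the only named stratum and four countries listed under Datasets to be analysed, a central shared list is quite possible, and Step 3 then applies.

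Nor does publication itself expose the block size to the sites at the start. The article is dated January 2023 and the intervention was planned from October 2022. Sites may have known the size from the full protocol, but that cannot be seen.

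It is also tempting to add that only about ten clusters are expected, so that a few steered classes would decide the trial. That rests on assumptions: 220·0.04 + 220·0.005 = 8.8 + 1.1 = 9.9 replaces the printed 0.05% by 0.5% and reads the 4% as a per-class proportion over the whole trial. The article calls it an infection rate in contacts, and the endpoint is per class and school week.

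All of this stands against the stronger reading. What survives is a stated choice: a small, apparently constant block in a design whose arms cannot be masked. The upper end is also not far-fetched. Randomisation is said to run within each school, schools join as units after an information session, and the enrolling centre oversees its schools. Consecutive entry of one school's classes is therefore plausible.

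**Conclusion.** The point holds as a minor one. Up to one allocation in three can be deduced, and a best guess can be right up to 71% of the time, by someone who knows the block size and sees the earlier arms in the same list. The upper limit applies if lists are kept per school or one centre enters a run of classes. It falls to a few percent or less if several sites interleave on one list.

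Harm needs two further conditions that the article does not state: single entry, and an order chosen by someone with a preference. Under those conditions baseline risk could become linked to arm, without correction by the primary test. No bias is shown and its size cannot be estimated from the documents. The point is a cheap improvement to the design.

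**What to change.** In Assignment to study groups, state that all consented classes of a school are registered and locked before any arm is released, and are then randomised together, in random order, within age stratum. This removes steering by order of entry within the batch and is the essential step.

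As a supplement, vary the block sizes at random and keep them out of documents that sites can read. On its own this is not enough, as Step 4 shows.

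No participants or data are added. The price is that a school's allocation waits until its class list is complete, and a class that joins later needs a later batch. The documents do not describe the module's capabilities, so whether this is a software change or a procedural rule for whoever submits the classes has to be checked. If the full protocol already works this way, a sentence saying so is sufficient.

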**Methods:**

In this cluster randomised trial protocol, we aim to determine whether the LM is useful to support schools opening and to reduce clusters and attack rates in schools, compared with the standard of care (SoC) surveillance by public health departments. This multicenter study will enrol 440 classes (around 8800 students, teachers and other personnel) from two countries, cluster randomised to LM or SoC. The samples from the pools will be collected and tested using PCR-based techniques. Test results will be combined with questionnaires filled in by children, parents, schoolteachers, and principals, concerning ongoing mitigation measures, their perceived psychological impact and other health and socio-economic information. An ancillary observational study will be carried out to study the prevalence of SARS-CoV-2 in schools, frequencies and size of clusters and attack rates, to compare the effectiveness of the different preventive measures adopted and to evaluate psychological issues in students and teachers in relation to the pandemic’s containment measures.

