#### Planned analyses

##### Datasets to be analysed, analysis populations

The analysed population consisted of pupils and students of kindergartens, primary and secondary schools located in Italy, Portugal, Germany and Mexico.

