##### Primary analysis (LM evaluation trial)

The number of clusters per class per week will be compared between the two arms: LM + SoC arm vs SoC only. Absolute and relative frequencies of clusters will be reported by arms and compared at univariate analysis with Chi Square or Fisher exact test, as appropriate. Univariate analysis will be performed and the p-values for statistical tests of associations of categorical and continuous variables with the two treatment arms will be reported (Chi square/Fisher exact test and T-test/Wilcoxon sum rank test for categorical and continuous variables, respectively). We will also investigate the psychological impact of Lolli tests and preventive measures to reduce the risk of infections; we will compare the frequency of infections according to socio-economic status, regions, teacher vs student, educational level, also taking into account vaccination rates within each class.

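### The protocol says classes are randomised within each school, but its allocation section names only age class as a stratum and its primary test uses neither factor

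*Protocol article*

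**What the plan says.** The general study design section (under Fig. 1) states the level of allocation: "classes will be randomised in each school to the adoption of the LM or to SoC". The section on assignment to study groups says how it is done. A web module takes the school-class identifier and returns an arm "based on a randomisation list balanced by four". It then adds: "The randomisation will be stratified according to age classes", with three age bands given as examples. School appears there only inside the class identifier. Country does not appear.

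In the primary analysis section, cluster frequencies by arm are "compared at univariate analysis with Chi Square or Fisher exact test, as appropriate". The sample size section uses an unstratified one-sided Z test: "a sample size of 440 classes (220 per arm) achieves 80% power to detect a difference between the group proportions of 3.5" per cent. The only adjustment stated for the trial comparison, in the section on missing data and drop-outs, is for response rates. Multivariable models are placed under the ancillary observational study.

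**The concern.** A programmer building the module from the allocation section would block by age class and not by school. That list does not deliver the within-school comparison described in the general design. By the protocol's own account, schools and countries differ in ways that bear on the outcome. Containment follows the national and regional rules in force, standard-of-care surveillance may change during the study, preventive measures differ between schools, and local mobility and public-health measures are treated as possible effect modifiers.

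What is at stake depends on which section governs. Without school in the list, both arms may be missing from a small school and chance imbalance in local epidemic level is not controlled. With school in the list, a test that ignores it uses too large a standard error. In either case the one declared stratum, age class, drops out of the primary test.

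**Working it through.** **The plan's own figure.** Inputs from the sample size section: 220 classes per arm, one-sided 5%, 80% power, pooled variance, 4% against a value 3.5 points lower. The formula is n = [1.645·√(2p̄q̄) + 0.842·√(p₁q₁ + p₂q₂)]² / (p₁ − p₂)².

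- 4% v 0.5%: p̄ = 0.0225, so n = (0.3450 + 0.1753)² / 0.035² = 221 per arm. Power at 220 is 79.9%, so the figure reproduces.
- The section prints the rates as "assumed to be 4% under the null hypothesis and 0.05% under the alternative hypothesis". With 0.05%, n = 157 and power at 220 is 90.5%, so it does not reproduce. That is a separate slip; 4% v 0.5% is used below.

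The formula has no term for school, country or age.

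**If the allocation section governs (age-only list).** Read balanced by four as permuted blocks of four, two per arm. Two classes in the same block share an arm with probability 1/3; in different blocks, 1/2. For a two-class school entered consecutively at a random point in the list, 3/4 × 1/3 + 1/4 × 1/2 = 0.375. If its classes are interleaved with those of other schools, the chance that all k classes share an arm approaches (1/2)^(k−1). Simulated values (classes per school and stratum are assumed, since the documents give none):

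| Classes in stratum | Entered consecutively | Interleaved |
|---|---|---|
| 2 | 37% | 49% |
| 3 | 8% | 24% |
| 4 | 1% | 12% |
| 5 | 0% | 6% |
| 6 | 0% | 3% |

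**If the general design governs (arms balanced within school).** With one yes/no outcome per class and a 4% rate in both arms, the unadjusted standard error is √(2 × 0.04 × 0.96 / 220) = 0.0187. Balance within school removes the between-school part, so the true variance is about (1 − ICC) times this. The effective one-sided critical value becomes 1.645/√(1 − ICC):

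- ICC 0.10: 1.645/√0.90 = 1.734, an upper tail of 4.1%.
- ICC 0.20: 1.645/√0.80 = 1.839, an upper tail of 3.3%.

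Simulation agrees: about 4% at ICC 0.10 and 3.0-3.3% at 0.20. Under the age-only list the unadjusted test kept a type I error of about 4-5%.

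**Power.** Simulation of 440 classes, 4% v 0.5%, beta-distributed school rates, ICC 0 to 0.2:

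| Allocation and test | 4 classes per school | 10 classes per school |
|---|---|---|
| Age-only list, unadjusted | 84-85% | 82-86% |
| Age-only list, school-stratified Mantel-Haenszel | 73-77% | 82% |
| Within-school balance, unadjusted | 85-87% | 83-86% |
| Within-school balance, school-stratified Mantel-Haenszel | 85-88% | 86% |

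The levels exceed the formula's 79.9% because the normal approximation is rough with about 220 × 0.005 = 1.1 events expected in one arm. The contrasts between rows are what matter. Comparing the last row with the first at the same ICC gives a gain of about 0-4 points.

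**The case against.** The strongest reply is that the two sections can be read together: allocation is within school, as the general design says, with age class as a further factor. The allocation section never says age class is the sole factor, the module receives the school identifier, and a journal article may omit details of the list. This stands to the extent that an age-only list is an inference. It does not remove the defect, because the section that specifies the list names its stratification factor and leaves out the one on which the general design depends.

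Two further points stand. The two-class school is a worst case, and nothing in the documents shows how common it is. An unadjusted test after stratified randomisation is valid, and model covariates are often left to an analysis plan. Here, though, the protocol names the primary test. Its comparisons by region and educational level, and its later stratification by class characteristics, are not that test.

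A reader might also infer that naming school as a stratum would by itself put both arms in every school. It would not: with blocks of four kept inside each school, two classes still share an arm with probability 1/3.

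Finally, a reader might infer an inflated type I error because the endpoint is counted per class per week. If about 24 weeks per class were treated as independent under an age-only list, the variance would be understated by 1 + 23 × ICC. At an assumed ICC of 0.05 that is 2.15, and a nominal two-sided 5% test would run at about 18% (1.96/√2.15 = 1.34). The documents do not establish this. They call classes the statistical units, size the trial on 220 classes per arm, and do not say that class-weeks enter the test as independent. That is a question about repeated observations, separate from this point.

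**Conclusion.** The point holds as an inconsistency in the allocation rule, together with a stated primary test that ignores both the declared age stratum and school. Its size is modest. The two consequences belong to different readings and should not be added together: whole-school allocation arises only if school is not in the list, and the conservative test only if arms are balanced within school.

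The documents do not support saying that schools will fall wholly in one arm, or that precision is badly lost. The first is a possibility mainly for schools with few classes in a stratum. The second amounts to about 0-4 power points for ICCs up to 0.2, with no inflation of type I error when there is one outcome per class. School sizes and ICCs are assumptions throughout.

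The abstract says "from two countries, cluster randomised to LM or SoC", while the analysis population lists "schools located in Italy, Portugal, Germany and Mexico". This is a further inconsistency. It leaves the role of country unclear but does not show that allocation is faulty.

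**What to change.** Make three changes together.

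1. Reconcile the general design and allocation sections by naming school as a randomisation stratum, with age class within it, and say whether country enters separately or only through school.
2. Specify a block size or constrained scheme that balances arms within small schools. Blocks of four alone do not guarantee this.
3. Replace the unadjusted primary test with one conditioned on the factors actually used in randomisation: a Mantel-Haenszel test or a regression stratified by age class, and by school where allocation is within school.

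The third change depends on the first. If the list turns out not to include school, adding school to the test lowered simulated power from 84-85% to 73-77% with four classes per school, so age class alone would be the stratum to use.

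The cost is small. The module already receives the school-class identifier, so the work is its configuration plus a few sentences of text. Arm totals may be slightly unequal. Single-class schools and schools with no clusters add nothing to a school-stratified test. At the planned rates only about 220 × 0.04 + 220 × 0.005 = 9.9 classes are expected to have an event, so many schools would have none. A Mantel-Haenszel test copes with such sparse strata better than a separate fixed effect for each school.
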